**Background of the study**

Cancer poses a considerable threat to global health and human life. The most recent data from the International Agency for Research on Cancer (IARC), part of the World Health Organization (WHO), indicates that in 2022, China experienced around 4.825 million new cancer cases and 2.574 million deaths attributed to cancer. These figures represent 24.2% of the global incidence and 26.4% of the global mortality associated with this disease[1]. With the rapid movement of China into an advanced stage of demographic aging, the need for palliative care within the health care system is growing. This has brought up a pressing need to enhance education and training for healthcare professionals[2,3]. Nursing students are expected to form the backbone of the future health workforce and are entrusted with the important task of providing professional end-of-life care (EOLC)[4]. By enhancing their education in palliative care, they will be able to develop a scientific perspective on death, establish positive life values, and acquire the necessary knowledge and skills to manage and adapt to death-related events, thus providing better care to patients and their families[5].Challenges of providing practical clinical education in palliative care to nursing students are distinct. Palliative care is a specialized medical field that involves proficiency in communication abilities for interactions with patients and healthcare professionals, compliance with ethics and morality as well as the complexity of end-of-life and death situations[6].Many students also become sad, afraid, and anxious upon initial exposure to EOLC, which demotivates them toward it[7]. Because these challenges in terms of emotional and education may hinder the development of their knowledge and professional ability in palliative care[8]. In view of the limitations of conventional educational approaches in meeting the dynamic needs of both education and practice in palliative care[9], there is a need to devise and implement some innovative educational models in this field.

With the help of computerized platforms, the integration of the latest developments in digital and virtual technologies introduces reconstructed scenarios observed in real life and simulates role plays.Virtual clinical simulation (VCS) marks one of the giant technological developments in the field of simulation.VCS creates immersive virtual environments for clinical training, featuring dynamic virtual patients, and allows students to engage in interactive simulations directly through their screens, offering students a simulated, hands-on experience within a controlled virtual setting[10].It is a learner-centered simulation methodology designed to develop decision-making, motor control, and communication skills, placing the individual at the core of the process[11]. VCS, as an innovative teaching approach, dynamically showcases the complex stages of EOLC, moving beyond traditional constraints of time, space, and resources to achieve educational outcomes not possible with previous models.In recent years,RCTs in countries like France, Portugal, and Singapore have implemented VCS for training nursing students. These studies have demonstrated that VCS training improves students' professional knowledge, learning satisfaction, and self-confidence, thereby enhancing their clinical judgment ability and positively impacting their clinical practice[12-14]. Integrating VCS into practical teaching substantially enhances the training abilities of students, closes the gap between theoretical learning and clinical application, and amplifies their practical and comprehensive care abilities. Nevertheless, in China, there exists a significant deficiency of interventional studies that concentrate on education in palliative care, particularly RCTs assessing the effectiveness of VCS in the training of nursing students.

**Methods**

#### Study design

This study is a prospective RCT implemented at a medical university in Southwest China. Nursing students taking the elective course "Cultural Perspectives on Death and End-of-Life Education" at the university's nursing department will be invited to participate.The study will randomly assign 96 participants into two distinct groups: a control group and an intervention group, each comprising 48 students. The control group will participate solely in conventional classroom teaching, whereas the intervention group will receive both conventional classroom teaching and enhanced learning through additional VCS.The purpose of this study is to explore whether VCS, compared to conventional teaching approaches, can enhance nursing students' knowledge, ability, and attitudes toward palliative care. The study procedure will follow the CONSORT flow diagram as shown in Fig 1.

[figure not shown]

#### Fig. 1 Flowchart of the study design

#### Randomization and blinding

Every student enrolled in the course will receive an invitation via email to join as research volunteers. Those who consent will participate in an initial meeting where they will sign informed consent forms. Subsequently, these volunteers will be asked to complete a detailed questionnaire that collects their sociodemographic data and academic performance, including their average course grades.This information will then be utilized to facilitate the randomization process. To preserve confidentiality, each student will choose a unique six-digit identifier. An impartial research assistant, who will not participate in the educational activities, will utilize SPSS 26.0 statistical software to allocate students evenly into either the control or intervention group with a 1:1 ratio.Seven days after their initial meeting，and following the completion of the randomization procedure, all students who will have volunteered for the study will be invited to meeting again. This subsequent meeting will be organized to conduct a comprehensive baseline evaluation of their knowledge, ability, and attitudes concerning palliative care.This initial assessment, referred to as the pre-intervention assessment, serves to establish a benchmark against which future improvements can be measured.During this meeting, participants will be informed of their group placement through their unique identifiers and will then be directed to the appropriate classrooms for a briefing on their respective group assignments.

Due to the specific nature of the intervention, conducting a double-blind trial will be deemed unfeasible. Nonetheless, a single-blind design will be implemented by keeping the group assignments hidden from both the research assistants and the instructors.

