#### Control Group

The control group will engage in conventional classroom teaching, which will last for 90 minutes and will be conducted by a seasoned lecturer with expertise in nursing. This teaching session will mirror the key points and utilize the same case themes as those found in the VCS system.

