#### Intervention Group

Participants in the intervention group will receive the same 90 minutes of classroom teaching as the control group, but they will additionally interact with a VCS system specifically developed for palliative care education by the research team.

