**Intervention content**

The VCS system leverages 3D modeling technologies via Java and VRML to craft immersive environments that mimic actual hospice settings, encompassing hospital wards, medical equipment, and representations of patients, their families, and healthcare workers. Participants will assume the role of virtual nurses, engaging with non-player characters (NPCs) to adeptly navigate patient care, thereby addressing both patient and family needs.After the 90-minute conventional classroom teaching, each participant will be assigned a unique code for accessing the VCS system, which will enable research assistants to effectively track participant engagement by monitoring their login activity on the system's backend.The VCS system is meticulously organized into three comprehensive modules: the Basic Knowledge Module, the Practice Theatre Module, and the Knowledge Testing Module.In the Basic Knowledge Module(Fig.2), participants will be introduced to basic knowledge about major concepts in palliative care. Learners will acquire a solid understanding of palliative care, its core principles, essential knowledge, psychological support for the terminally ill patient, guidelines for counselling the grieving, recognition of common clinical presentation at the end of life, and updates on EOLC practices.The Practice Theatre Module focuses on the case of an 89-year-old elderly male patient with advanced lung cancer who is admitted to a palliative care ward for hospice care(Fig. 3).This module features six detailed learning scenarios: Case Introduction, Admission Care, Specialized Nursing, Spiritual Care, Social Support, and EOLC.Each scenario includes a variety of contextual educational tasks such as choices, dialogues, and reading assignments, engaging learners in decision-making processes. Learners will interact with the VCS environment by clicking on navigation icons and using menu controls on the screen, guided by an automated assistant. Additionally, the system will evaluate the "correctness" of each task choice, assign scores, and automatically log these data in the backend.Such interactions will empower virtual nurses to perform assessments, physical exams, select medical tools, execute appropriate interventions, and maintain effective communication. The overarching aim is to enhance terminally ill patients' quality of life. Furthermore, this module will seek to cultivate a compassionate attitude and holistic palliative care ability among students, thus enabling them to promptly and accurately identify and address the physiological, psychological, and emotional issues of terminally ill patients when faced with end-of-life situations. It will also promote the development of critical clinical thinking and ethical decision-making abilities. The Knowledge Testing Module will present 10 randomized questions, awarding 1 point for each correct response(Fig. 4).The system will generate experimental reports based on different scenarios, which encompass the correct task answers, the options selected by users, and their final scores.These reports will specify the steps or knowledge points that remain incomplete, and can be readily archived by users for future reference when conducting additional experiments. Furthermore, these reports will offer invaluable insights to facilitate students' reflective learning processes.

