**Sample Size**
The determination of the necessary sample size for this investigation was conducted conducted using G*Power 3.1.9 software[15],employing a two-tailed independent t-test with an alpha level of 0.05, a power of 0.90, and an effect size of 0.71[16]. Taking into account a 10% attrition rate，at least 48 students per group were needed to achieve this statistical power for the study.

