**Data Analysis**
We will use SPSS 26.0 statistical software to analyze the data. When the data follow a normal distribution, descriptive statistics (mean and standard deviation) will be used to represent the central tendency and dispersion for continuous demographic data (e.g., age), as well as for ratings of palliative care knowledge, ability, and attitudes. For data that do not follow a normal distribution, the median and interquartile range will be utilized to depict central tendency and variability.We will use frequencies and percentages to represent categorical data, such as gender. Independent t-tests will be used to examine whether there are significant differences in the mean demographic data between the intervention and control groups. Chi-square tests will be employed to compare the distribution of sample characteristics between the two groups for homogeneity. Independent t-tests will also be used to compare the levels of palliative care knowledge, ability, and attitudes between the intervention and control groups. To compare the overall scores and scores across different dimensions of palliative care knowledge, ability, and attitudes before and after the VCS education system intervention, researchers will use paired t-tests to assess the changes in these levels in the students. A two-tailed p<0.05 is considered statistically significant.

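### Students learn their group and are briefed by group before the lesson both arms share, and the protocol does not require that lesson to be taught jointly or by one lecturer

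*Protocol*

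**What the plan says.** Protocol, Randomization and blinding: students are individually randomised 1:1. Seven days after the first meeting they return for the pre-intervention assessment (T0). At that meeting "participants will be informed of their group placement through their unique identifiers and will then be directed to the appropriate classrooms". The sentence continues beyond this quote and gives the purpose of the classrooms as a briefing on the group assignment. The same section says that allocation is to be kept from the research assistants and the instructors.

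Protocol, Control Group: the conventional lesson lasts 90 minutes and "will be conducted by a seasoned lecturer with expertise in nursing".

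Protocol, Intervention Group: "Participants in the intervention group will receive the same 90 minutes of classroom teaching as the control group". No lecturer, room, time or sitting is given for this arm.

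Protocol, Intervention content: "After the 90-minute conventional classroom teaching, each participant will be assigned a unique code for accessing the VCS system". The planned treatments therefore diverge only once the lesson is over.

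Protocol, Data Analysis: "Independent t-tests will also be used to compare the levels of palliative care knowledge, ability, and attitudes between the intervention and control groups". No term for class or sitting is mentioned.

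**The concern.** The lesson is meant to be the constant part of the comparison, so that the arms differ only in VCS. That holds only if the lesson reaches both arms alike. The protocol weakens this in two ways.

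- **Timing of disclosure.** Students know their group, and have been briefed by group, before they sit the lesson. Those expecting VCS and those not expecting it may bring different effort or attention to it. Instructors who are supposed to be unaware of allocation then teach students who know theirs.
- **Delivery of the lesson.** Staff could follow the text exactly and teach one class per arm, with the same or different lecturers. Lecturer, time of day, questions asked and class atmosphere would then coincide completely with arm. A difference between the two classes would be read as a VCS effect, or would mask one, on all three primary outcomes. No later analysis could undo that, and more students per class would not help.

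**Working it through.** **1. The plan's own figure.** Inputs from Sample Size: "employing a two-tailed independent t-test with an alpha level of 0.05, a power of 0.90, and an effect size of 0.71"; "Taking into account a 10% attrition rate"; "at least 48 students per group were needed". For a two-sided two-sample t-test, the noncentrality is 0.71 × √(n/2). With n = 43 it is 0.71 × √21.5 = 3.29 on 84 degrees of freedom, and power is 0.902. Then 43 / (1 − 0.10) = 47.8, rounded up to 48. The stated sample size reproduces, and the point below is not about arithmetic.

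**2. Order of events.** T0 is labelled pre-intervention and disclosure happens at the T0 meeting. The lesson is part of what each arm then receives, and VCS access follows the lesson. The sequence is therefore: T0 and disclosure, group briefing, lesson, VCS codes (intervention arm), T1. Disclosure and the split into group rooms come before the one component that should be identical.

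**3. What the text fixes about the lesson.**

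| Feature | Control arm | Intervention arm |
|---|---|---|
| Length | 90 minutes | the same 90 minutes |
| Content | key points and case themes matched to the VCS system | the same teaching as control |
| Lecturer | one experienced nursing lecturer | not stated |
| Room, time, joint or separate sitting | not stated | not stated |

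Both one joint lesson and two arm-specific lessons comply with this.

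**4. Illustration if there were one class per arm.** Assumptions, none of them from the documents: each arm has its own single sitting, VCS has no effect, total outcome variance is 1, and a share ICC of it is due to the sitting. With n = 43 analysed per arm (step 1):

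- true variance of the difference in means = 2·ICC + 2(1 − ICC)/n
- variance that the t-test estimates = 2(1 − ICC)/n
- ratio of true to assumed standard error: k = √(1 + n·ICC/(1 − ICC))
- type I error = 2 × P(T > 1.989/k), with T on 84 degrees of freedom
- SD of the spurious between-arm difference = √(2·ICC)

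| ICC (assumed) | k | 1.989/k | Type I error | SD of spurious difference |
|---|---|---|---|---|
| 0.01 | √(1 + 0.43/0.99) = 1.20 | 1.66 | 10% | 0.14 |
| 0.02 | √(1 + 0.86/0.98) = 1.37 | 1.45 | 15% | 0.20 |
| 0.05 | √(1 + 2.15/0.95) = 1.81 | 1.10 | 27% | 0.32 |
| 0.10 | √(1 + 4.30/0.90) = 2.40 | 0.83 | 41% | 0.45 |

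The last column is in outcome SDs and can be set against the planned effect of 0.71. Without an ICC, a fixed difference between the two sittings of 0.2 SD (noncentrality 0.2 × √21.5 = 0.93) gives a rejection rate of 15%, and 0.3 SD (1.39) gives 28%.

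**5. If the lesson is joint.** Both arms share the sitting, its effect cancels from the difference, and the rate stays at 5% as far as this source is concerned.

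**The case against.** A reader might infer from the group-specific classrooms that the lesson itself is taught to each arm separately. The documents do not support that. The rooms are stated to be for a briefing, and no section places the 90-minute lesson in them. The wording for the intervention arm, "Participants in the intervention group will receive the same 90 minutes of classroom teaching as the control group", fits a single shared session. Describing each arm under its own heading is ordinary protocol layout. The plural used for instructors in the blinding paragraph does not show different lecturers per arm, and the Control Group section refers to a single lecturer. Keeping allocation from instructors also sits more easily with a mixed room, although it does not settle the matter. The flow diagram (Fig. 1) is not available here and might show where the arms part.

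The size is open to objection too. The documents give no ICC. Individual randomisation balances class composition in expectation, so only differences arising around one 90-minute session could contribute. Nothing in the documents supports the upper end of the assumed range.

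All of this stands, and it makes the confounding conditional. It does not remove the point. The available text nowhere requires a common sitting or lecturer, and disclosure before the shared lesson is stated outright. Nor is this a detail to leave to an analysis plan, because complete confounding of class with arm cannot be repaired in analysis.

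**Conclusion.** The point holds in a limited form. The protocol discloses allocation and briefs students by group before the lesson that both arms share, and it does not fix joint delivery of that lesson or a common lecturer. Whether sitting is in fact confounded with VCS depends on how the lesson is delivered, which the text leaves open. If there is one class per arm, the confounding is complete. The type I error would then be about 10% at an ICC of 0.01 and 27% at 0.05, with 43 analysed per arm; these figures only illustrate assumed values. If the lesson is joint, there is no inflation from this source. The effect of early disclosure on effort in the lesson and on instructor blinding does not depend on separate classes, but the documents offer no basis for putting a number on it. The sample size calculation is unaffected. The change is worth making before teaching starts, because the risk cannot be corrected afterwards and the remedy is cheap.

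**What to change.** - **Control Group and Intervention Group:** state that both arms attend the same 90-minute lesson together, in one sitting with one lecturer. If room size forces two sittings, mix both arms in each, use the same lecturer for both, and include sitting as a factor in the between-group comparison under Data Analysis.
- **Randomization and blinding:** keep the T0 assessment where it is, but move group disclosure and the group briefing to after the lesson, when VCS codes are issued.

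This costs protocol wording plus a room for 96 students, or two mixed sittings. It needs no extra students or measurements. If a joint lesson is already intended, stating it costs nothing, and moving the disclosure step is the only change in conduct.

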**Data Collection**
Data Collection

Seven days after their initial meeting, both groups will undergo baseline assessments of their palliative care knowledge, ability, and attitudes (pre-intervention, T0). After the intervention, post-intervention assessments (T1) will be conducted to evaluate the participants' palliative care knowledge, ability and attitudes. In addition, students in the intervention group will be invited to complete the Student Satisfaction and Self-confidence in Learning Scale at the end of the intervention.Following the T1 assessment, the control group will receive the same VCS intervention as the intervention group.

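### The protocol says research assistants are blinded to allocation, but its own procedures reveal the arm to them; instructor blinding is unprotected, and the single-blind label misleads

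*Protocol*

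**What the plan says.** Under Randomization and blinding, the protocol rules out a double-blind trial and says instead that "a single-blind design will be implemented by keeping the group assignments hidden from both the research assistants and the instructors". It makes no exception for any assistant or instructor.

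Other provisions bear on that sentence:

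- **Allocation** (same section): "An impartial research assistant, who will not participate in the educational activities, will utilize SPSS 26.0 statistical software to allocate students evenly".
- **Disclosure** (same section): at the meeting that holds the baseline assessment (T0), "participants will be informed of their group placement through their unique identifiers". Students are then "directed to the appropriate classrooms for a briefing on their respective group assignments".
- **Log-in tracking** (Intervention content): after the 90-minute lesson each participant gets an individual VCS code, "which will enable research assistants to effectively track participant engagement by monitoring their login activity on the system's backend".
- **Control access** (Data Collection): "Following the T1 assessment, the control group will receive the same VCS intervention as the intervention group".
- **Satisfaction scale** (Data Collection): at the end of the intervention, "students in the intervention group will be invited to complete the Student Satisfaction and Self-confidence in Learning Scale".

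The Control Group and Intervention Group sections give both arms the same 90-minute lesson. Before T1 the arms differ only in VCS.

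**The concern.** A blinding statement tells readers which sources of bias have been closed off. If the named staff can see the arm in the course of their ordinary duties, readers will credit a protection that the trial lacks.

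The practical exposure has two parts. An assistant who knows the arm and also administers or scores T0 or T1 could prompt, clarify or score differently by arm. And if allocation is known during a lesson meant to be identical in both arms, teaching emphasis and student effort can differ by arm before VCS has begun. Any such difference would then be counted as an effect of VCS.

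**Working it through.** No arithmetic is needed to establish the conflict. The check sets the blinding claim beside the prescribed procedures, role by role.

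**Research assistants: contradicted.**
1. A research assistant runs the allocation, so at least one knows every assignment.
2. Research assistants, in the plural, monitor VCS log-ins by individual code. Controls receive VCS only after T1, so any student with log-in activity before T1 is in the intervention arm.
3. The satisfaction scale goes to one arm only. Whoever distributes or collects it sees that arm.
4. The protocol does not separate assistants who allocate, track log-ins or handle that scale from those who administer or score the T0 and T1 primary outcomes. It names no blinded assessor.

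**Instructors: unprotected.**
1. Students learn their group at the baseline meeting and go to group-specific briefings.
2. The text does not say who gives the briefings, whether the lesson is taught in those rooms, or whether the arms are taught together.
3. VCS codes are issued only after the lesson, so the lesson itself does not require anyone to know the arm.
4. Blinded instructors are therefore possible under the text, but nothing secures it.

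**Students: open-label, with no claim to the contrary.** They are told their group. The protocol does not say they are blinded. Disclosure falls at the same meeting as T0, and the text does not fix that T0 is finished first.

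**Size.** The documents give no figure for any bias. As an illustration only, take the planned two-sided t-test, no true effect, one endpoint, and an assumed bias of *b* standard deviations (SD).

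- The protocol's sample size reproduces: *d* = 0.71, two-sided alpha 0.05 and power 0.90 give 42.67, so 43 per arm. With 10% attrition, 43 / 0.90 = 47.8, so 48.
- The chance of p < 0.05 is P(|T| > t(0.975; 2n − 2)), where T is noncentral t with noncentrality b × √(n/2). For n = 43 and b = 0.2 the noncentrality is 0.2 × √21.5 = 0.93.

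| Assumed bias (SD) | 43 per arm | 48 per arm |
|---|---|---|
| 0 | 5.0% | 5.0% |
| 0.1 | 7.4% | 7.7% |
| 0.2 | 15.0% | 16.3% |
| 0.3 | 28.0% | 30.7% |

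These rows show how sensitive the test is to a bias of a given size. They do not separate avoidable from inherent bias, so they do not measure what the fix would gain.

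**The case against.** The strongest reply is that the protocol already has safeguards. The allocating assistant is described as impartial and takes no part in teaching. Students use self-chosen six-digit identifiers. Whoever runs an allocation will normally know it, and the protocol does not say that this person collects outcomes or that VCS codes link to the questionnaires. If students complete the instruments themselves, as their titles suggest, assistants have limited room to influence them. Controls also get VCS after T1, which tempers any disappointment.

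This lowers the likely harm but does not rescue the sentence, which covers all assistants without exception. Staying out of teaching is not staying out of outcome collection, and the identifiers are the means by which groups are announced.

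Three stronger readings are tempting and should be resisted:

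- *Telling students their group contradicts the plan.* It does not: the protocol names assistants and instructors as the blinded parties and concedes that double-blinding is unfeasible.
- *Instructors are shown to be unblinded.* They are not. That would be an inference from the group briefings, and a joint lesson also fits the text.
- *The error rate rises to 15% or 28%.* Those figures rest on assumed biases that no document supports.

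Blinding of the analyst may be covered in the statistical analysis plan, which is not shown, so its absence here is not part of this point.

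**Conclusion.** The point holds in three graded parts. The claim that research assistants are blinded is wrong as written; this rests on the text alone. The claim that instructors are blinded is neither contradicted nor protected. The single-blind label misleads, because participants know their arm and the substitute meaning (blinded assistants and instructors) fails for the assistants.

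The size of the avoidable bias cannot be derived from the documents. Bias that arises because students know by T1 that they used VCS is inherent in the comparison and will remain whatever is changed. The case for acting rests on the false statement of protection and the low cost of correction, not on a calculated inflation of the error rate. The change should be made before the first lesson, because conduct cannot be repaired afterwards.

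**What to change.** 1. **Order of events.** Complete T0, then teach the identical 90-minute lesson to both arms together or in sessions that mix the arms. Disclose allocation only after that, and issue VCS codes individually. Drop the group briefings before the lesson. Lecturer and students are then blind during the shared lesson, and session effects cannot line up with arm.
2. **Roles.** Use existing assistants in separate roles. Those who allocate, track log-ins or handle the satisfaction scale should not administer or score the T0 and T1 primary outcomes.
3. **Wording.** Replace the single-blind label with a statement that the trial is open-label to participants after disclosure. List which staff are and are not blinded, and claim blinding only for roles that step 2 protects. A general claim that everyone handling outcomes is blinded would fail again, because the satisfaction scale goes to one arm only.

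The cost is one reordered step, a division of tasks and revised text. The downsides are a larger or mixed class and later disclosure to students. The sample size of 48 per arm is unaffected.
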